9.1 Data Collection16

9.2 Data Retention16

**10 SAMPLE SIZE** 16

**11 REFERENCE**17

**12 APPENDIX**18

1. **BACKGROUND**

Acute myeloid leukemia (AML) is a heterogeneous hematologic malignancy characterized by abnormal proliferation, differentiation, and clonal expansion of hematopoietic stem/progenitor cells that invade the bone marrow, blood, and extramedullary tissues. Allogeneic hematopoietic stem cell transplantation (allo-HSCT) is currently the primary curative approach for relapsed/refractory AML, but more than 30% of AML patients experience post-transplant relapse. Relapsed patients have a poor prognosis, with a two-year overall survival rate of less than 15%, and relapse is a major cause of post-transplant mortality(1). High-risk factors for relapse include complex karyotype, TP53 gene mutations, failure to achieve complete remission after two cycles of induction chemotherapy, and minimal residual disease (MRD) positivity before transplantation. Despite allo-HSCT being the primary curative approach for relapsed/refractory AML, more than 30% of patients relapse after transplant. The prognosis for relapsed patients remains poor, with a two-year overall survival rate of less than 15%, making relapse the leading cause of post-transplant mortality(2). So far, the main strategies for preventing post-transplant relapse include optimizing conditioning regimens, improving GvHD prevention protocols, post-transplant maintenance therapy, and prophylactic donor lymphocyte infusion (DLI)(3).

DNT cells are a subset of mature T lymphocytes, constituting about 1-5% of peripheral blood mononuclear cells (PBMC) in mice, rats, and humans. DNT cells express CD3 and γδ-TCR but do not express CD4, CD8, or NK cell markers, nor do they bind to the invariant natural killer T cell (iNKT)-specific αGalCer-loaded CD1d tetramer(4). Therefore, they are distinct from conventional T cells, NK cells, and NKT cells. [name]’s laboratory at the University of Toronto was the first in the world to report the characteristics of antigen-specific DNT cells with transplant immune tolerance, and they conducted extensive studies on how these cells differ from traditional CD4^+^ or CD8^+^ T cells. Notably, transplantation of allogeneic DNT cells into mice not only did not induce graft-versus-host disease (GvHD) but also suppressed GvHD caused by allogeneic CD4^+^ and CD8^+^ T cells(5).

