**2.2 Secondary Objectives**

- Pharmacokinetics (PK) indicator (Cmax)

The peak concentration of allo-DNT cells amplified in the peripheral blood (Cmax, detected by Flow Cytometry). Time Frame: Up to 2 years.

- Pharmacokinetics (PK) indicator (AUC)

Allo-DNT cells blood concentrations will be measured at different time points to evaluate the area under the curve (AUC). (AUC, detected by Flow Cytometry). Time Frame: Up to 2 years.

- Pharmacokinetics (PK) indicator (Tmax)

Allo-DNT cells blood concentrations will be measured at different time points to evaluate the peak time (Tmax) in peripheral blood. Tmax is defined as the time to reach the highest concentration (Tmax, detected by Flow Cytometry). Time Frame: Up to 2 years.

- Pharmacokinetics (PK) indicator (T1/2)

Allo-DNT cells blood concentrations will be measured at different time points to evaluate the elimination half-life in hours (T1/2). T1/2 is defined as the time point when the concentration of allo-DNT reaches half of maximum in a patient’s peripheral blood (T1/2, detected by Flow Cytometry). Time Frame: Up to 2 years.

- Recurrence rate at 6 months

Record the proportion of patients with recurrence in the study. Time Frame: Up to 6 months.

- Relapse-free survival (RFS)

Relapse-free survival is the time from study enrollment until documented disease relapse, or death from any cause. Time Frame: Up to 2 years.

- GvHD-free and relapse-free survival (GRFS)

GRFS is the time from study enrollment until documented disease relapse, or death, or GvHD occur from any cause. Time Frame: Up to 2 years.

- 2-year overall survival

From the date of entry into the clinical study until death from any cause. Time Frame: Up to 2 years.

1. **TRIAL DESIGN**

The trial is divided into two parts: Part A is a dose escalation trial with two dose groups (1.0×10^8 cells/kg, 1.5×10^8 cells/kg at day 0, day 28 and day 56), with 6-12 patients planned to be enrolled. Part B is a dose-expansion randomized controlled trial in which 40-60 patients will receive RC1012 infusions at recommended phase II dose (RP2D) levels. Patients at the end of the infusion will continue to be followed up for a total of 2 year.

1. **ELIGIBILITY**
   1. **Subject Eligibility**
      1. **Inclusion Criteria**

- Voluntarily sign an ICF and expect to complete the study procedures for follow-up examinations and treatment.
- Aged 18 to 70 years (including cut-offs), regardless of gender.

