- Serum Cytokine Levels: Cytokines will be measured before infusion of DNTs, then 6, 24, 48 hours, 5d, 7d after each DNT infusion, and 14d, 21d, 28d after the 3^rd^ infusion. Serum cytokines included interleukin-6 (IL-6), interferon (IFN)-γ, IL-8, IL-10, tumor necrosis factor (TNF)-α, macrophage inflammatory protein (MIP)-1α, MIP-1β, monocyte chemoattractant protein (MCP-1), and soluble receptors IL-1Rα and IL-2Rα.
- Assessment of DNTs in vivo: Peripheral blood aspirates will be analyzed by FACS to assess and quantify the percentages of DNTs before infusion, then 6, 24, 48 hours, 5d, 7d after each DNT infusion, and 14d, 21d, 28d after the 3^rd^ infusion.
- Electrocardiogram (ECG): ECGs should be performed when clinically indicated.
- Bone Marrow Analysis: Bone marrow aspirates will be obtained before the first cycle of DNTs therapy and 28 days after the 3^rd^ infusion. After achieving CR, analyze once a month.
  1. **Follow-up**

Patients will be followed-up for survival data for 2 year from the date of start of treatment. Blood routine, biochemistry and bone marrow studies will be obtained monthly as clinically indicated to assess disease. Analyses will include morphologic examination of the aspirate, FACS, and cytogenetics when indicated.

1. **TREATMENT RESPONSE/OUTCOME ASSESSMENT**
   1. **Main Outcome Measurement**

Cumulative relapse rate at 6 months post-treatment.

- 1. **Secondary Outcome Measurement**

Relapse-free survival (RFS), GvHD-free relapse-free survival (GRFS), and 2-year overall survival (OS) post-cell infusion.

- 1. **Safety Measurement**
- Safety assessment indicators include vital signs, clinical laboratory tests (complete blood count, blood biochemistry, coagulation function, urinalysis), 12-lead electrocardiogram (ECG), and physical examination. Throughout the study, research center staff will monitor adverse events.
- Adverse Events (AEs): The occurrence of all AEs and serious adverse events (SAEs) will be tracked. Changes from baseline in laboratory tests (including complete blood count, urinalysis, blood biochemistry, coagulation function), 12-lead ECG, physical examination, and vital signs (temperature, respiration, blood pressure, and pulse) will be analyzed.

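### Section 2.2 labels T1/2 an elimination half-life but defines it as the time at half of maximum, and the assay in section 5.3 reports percentages of DNTs rather than the concentrations this needs

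*Protocol*

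**What the plan says.** Protocol section 2.2 lists four pharmacokinetic indicators as secondary objectives: Cmax, AUC, Tmax and T1/2. All are detected by flow cytometry and all have a two-year time frame.

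- For T1/2 the aim is "to evaluate the elimination half-life in hours (T1/2"), and the next sentence gives the operating rule: "T1/2 is defined as the time point when the concentration of allo-DNT reaches half of maximum".
- Tmax is a separate indicator: "Tmax is defined as the time to reach the highest concentration". Cmax is described as "The peak concentration of allo-DNT cells amplified in the peripheral blood", so a rise after infusion is contemplated.
- The quantity named throughout section 2.2 is a blood concentration of allo-DNT cells.

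Section 5.3 is the only description of the assay: "Peripheral blood aspirates will be analyzed by FACS to assess and quantify the percentages of DNTs before infusion". Samples follow at 6, 24 and 48 hours, and then at "5d, 7d after each DNT infusion, and 14d, 21d, 28d after the 3^rd^ infusion". Section 3 gives three infusions per patient ("1.5×10^8 cells/kg at day 0, day 28 and day 56" for the higher dose group). Section 1 describes DNTs as "constituting about 1-5% of peripheral blood mononuclear cells (PBMC) in mice, rats, and humans".

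**The concern.** An elimination half-life describes how fast the signal falls and does not depend on when the peak occurred. The time at which the signal stands at half of its maximum depends on both. Two patients with identical decline but different peak times would be given different half-lives, so differences in Tmax would appear as differences in persistence. As worded, the rule could also be met before the peak, and after any of the three infusions.

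The measurand is a second problem. A percentage is not a concentration: it moves when the other cells in its denominator move, and these patients are 60 to 100 days past transplant at entry. The protocol states no absolute count, no marker for infused cells and no use of the pre-infusion sample as a baseline. Cmax and AUC are affected as well as T1/2.

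At stake is whether the reported persistence and exposure mean what their labels say. In Part A these summaries would rest on 6 to 12 patients over two dose groups, where a few distorted values carry weight.

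**Working it through.** The protocol states no half-life, Tmax or expected DNT level after infusion, so there is no figure to reproduce. The Tmax, half-life and signal values below are assumptions chosen to show a range.

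**1. What the definition returns.** Take time from the infusion and let the concentration fall from the peak as C(t) = Cmax × 2^(−(t − Tmax)/h), where h is the true half-life. Setting C(t) = Cmax/2 gives t = Tmax + h. The ratio to the true value is 1 + Tmax/h.

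| Assumed Tmax | h = 24 h | h = 48 h | h = 120 h |
|---|---|---|---|
| 0 h | 24 h (1.0) | 48 h (1.0) | 120 h (1.0) |
| 6 h | 30 h (1.25) | 54 h (1.125) | 126 h (1.05) |
| 24 h | 48 h (2.0) | 72 h (1.5) | 144 h (1.2) |
| 48 h | 72 h (3.0) | 96 h (2.0) | 168 h (1.4) |

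The definition is right only in the first row. The first scheduled post-infusion sample is at 6 h, so an observed peak cannot fall earlier than the second row.

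**2. The rising limb.** If the rise to the peak were linear, half of maximum would first be met at Tmax/2, for example at 12 h for a Tmax of 24 h. The definition sentence does not exclude this reading.

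**3. Which infusion can support a slope.** After infusions 1 and 2 the scheduled post-infusion times are 6, 24 and 48 h, 5 d and 7 d. With a peak at 48 h, only the 5 d and 7 d samples lie beyond it. After infusion 3 the series continues to 14, 21 and 28 d, so the same peak leaves five later samples (5, 7, 14, 21 and 28 d).

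**4. Concentration against percentage.** Section 2.2 asks for the concentration of allo-DNT cells; section 5.3 delivers the percentage of DNTs, and its denominator is not stated. Whether resident DNTs enter that percentage is also not stated. *If* they do, as a constant background b added to an infused signal A × 2^(−t/h) that peaks at time zero, half of the total maximum is reached when b + A × 2^(−t/h) = (b + A)/2. This gives t = h × log2[2A/(A − b)]. With h = 48 h and A = 10 percentage points:

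- b = 1: 48 × log2(20/9) = 55.3 h
- b = 3: 48 × log2(20/7) = 72.7 h
- b = 5: 48 × log2(20/5) = 96 h

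If A is no larger than b, half of maximum is never reached. The values of b span the general 1–5% range in section 1.

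**5. Time frame.** The third infusion is on day 56 and the last scheduled DNT sample is 28 days later: 56 + 28 = day 84. Section 5.4 mentions FACS during later follow-up, but for disease assessment and without naming DNTs.

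**The case against.** The strongest reply is that this is loose wording on a secondary parameter. The sentence before the definition says elimination, so a pharmacokineticist would read the declining limb and ignore the rising one. If the peak comes early, the error is small: 54 h against 48 h when Tmax is 6 h. Slope-fitting rules, minimum numbers of points and baseline handling commonly sit in a statistical analysis plan, which is not at hand. The two-year time frame is an outer limit and biases nothing.

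Much of this stands. The rising-limb reading is possible but strained, the error can be modest, and the time frame is only a matter of alignment. It does not rescue the definition itself. The protocol did not leave the rule to a later document; it fixed one, and an analysis plan using a terminal slope would contradict it.

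Two stronger readings are tempting, and the document supports neither.

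- A reader might infer that the measured percentages include the patient's own DNTs. Section 2.2 names allo-DNT cells as the target and the flow panel is not described, so what can be said is that no method of separation is stated. With complete donor chimerism required at entry, resident DNTs would in any case be largely of transplant-donor origin. The 1–5% figure is a general one for three species, not for patients soon after transplant, and need not share the assay's denominator.
- A reader might infer that a wrong half-life would misdirect repeat dosing. No section uses pharmacokinetics for a dosing decision: the infusion days are fixed and the MTD rests on DLTs.

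**Conclusion.** The definition of T1/2 is wrong as written. It contradicts the name of the parameter and, under first-order decline, exceeds the half-life by Tmax. For an assumed true half-life of 48 h the excess is 6 h at a Tmax of 6 h (12.5%), 24 h at 24 h (50%) and 48 h at 48 h (100%). These sizes rest on assumed values and on a mono-exponential fall from the peak; the protocol supplies neither.

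The mismatch between concentration in section 2.2 and percentage in section 5.3 is also in the text and touches Cmax and AUC. How far resident cells distort the values cannot be determined from the protocol; the background calculation is conditional. The consequences are confined to secondary pharmacokinetic endpoints. The definition should be corrected because following it literally gives a mislabelled result and the repair is cheap.

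**What to change.** - **T1/2.** Define it as ln2/lambda_z, with lambda_z the log-linear slope over the post-peak declining phase after a named infusion. Infusion 3 is the natural choice, since its sampling runs to 28 days. Report it as not estimable with fewer than three post-peak samples. Alternatively, keep a half-of-maximum rule but relabel the quantity as time from Tmax to half of Cmax.
- **Measurand.** Reconcile sections 2.2 and 5.3 by reporting an absolute DNT count: the FACS percentage multiplied by the cell count that matches the gate's denominator, with that denominator stated. A lymphocyte count is right only if the percentage is of lymphocytes.
- **Infused against resident cells.** State whether the flow panel identifies infused cells. If it cannot, correct by the sample taken before the first infusion. Samples before infusions 2 and 3 may still contain infused cells and would over-correct. A fixed baseline does not remove a background that rises as counts recover, and the report should say so.
- **Time frame.** Change the pharmacokinetic time frame to 28 days after the third infusion.

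The cost is mostly wording. The one practical addition is a paired blood count at DNT sampling times where none is already drawn: section 5.3 schedules haematology two to three times a week, which does not guarantee counts at 6, 24 and 48 h.

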- Subject must be diagnosed with AML according to World Health Organization (WHO) criteria (2016).
- The subject has received an allo-HSCT within 60-100 days, the percentage of malignant primitive cells in the bone marrow is < 5% after HSCT and STR-PCR shows complete donor chimerism.
- The subject has one of the following high-risk factors for relapse after allo-HSCT: (1) Failure to achieve remission after two courses of induction chemotherapy. (2) Prior history of Myelodysplastic Syndromes (MDS) or Myeloproliferative Neoplasm (MPN). (3) High leukocytes (≥100×10^9/L) combined with Central Nervous System Leukemia (CNSL); (4) Positive Minimal Residual Disease (MRD) before HSCT; (5) Non-remission or disease progression prior to HSCT; (6) Subject with cytogenetic high-risk factors (except that who can be treated with targeted drugs).
- The subject has recovered from the toxicity of the prior treatment, i.e., CTCAE toxicity grade <2 (unless the abnormality is tumor-related).
- ECOG score 0 to 1.
- With appropriate organ function:
- • Glutathione aminotransferase (AST) ≤ 3 times the upper limit of normal (ULN);
- • Glutamic aminotransferase (ALT) ≤ 3 times ULN;
- • Total bilirubin ≤ 1.5 times ULN, unless the patient has documented Gilbert syndrome. Patients with Gilbert-Meulengracht syndrome with total bilirubin ≤ 3.0 times ULN and direct bilirubin ≤ 1.5 times ULN may be included;
- • Serum creatinine ≤ 1.5 times ULN or a creatinine clearance ≥ 60 ml/min;
- • Hemoglobin ≥ 80 g/L or hemoglobin maintained at that level following transfusion;
- • International Normalized Ratio (INR) ≤ 1.5 times ULN and Activated Partial Thromboplastin Time (APTT) ≤ 1.5 times ULN;
- • Absolute neutrophil count (ANC) ≥ 1.5 x 10^9/L.
- • A platelet count ≥ 50 x 10^9/L or a platelet count maintained at that level following a platelet transfusion;
- • Left ventricular ejection fraction (LVEF) ≥ 45%.
- Female patients with childbearing potential should have a negative pregnancy test during the screening period. Any male and female patients of childbearing potential must agree to use an effective contraception method for at least six months from the time that they sign the informed consent form until the end of the cell infusion. Female patients without childbearing potential (meeting at least 1 of the following criteria) is described below.
- • Have undergone a hysterectomy or bilateral oophorectomy;
- • Medically recognized as ovarian failure;

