- • Medically recognized as post-menopausal (at least 12 consecutive months of menopause without pathological or physiological cause).
  - 1. **Exclusion Criteria**
- Patients with active grade II to IV acute GvHD or extensive chronic GvHD.
- Subject is confirmed to have morphological relapse of leukemia or positive MRD after allo-HSCT.
- Subject with extramedullary infiltration of leukemia.
- Suffer from other malignancies within 5 years prior to screening, except adequately treated carcinoma in situ of the cervix, basal cell or squamous epithelial cell skin cancer, post-radical thyroid cancer, and post-radical ductal carcinoma in situ.
- Has severe respiratory disease (previous or combined history of severe interstitial lung disease, severe chronic obstructive pulmonary disease, severe pulmonary insufficiency, symptomatic bronchospasm).
- A previous history of a definite neurological or psychiatric disorder, including epilepsy or dementia.
- Evidence of active central nervous system invasion or cranial neuropathy.
- Patients with positive hepatitis B surface antigen (HBsAg) or hepatitis B core antibody (HBcAb) and peripheral blood hepatitis B virus (HBV) DNA titration assay not within the normal reference range, positive hepatitis C virus (HCV) antibody and peripheral blood HCV RNA ,positive for human immunodeficiency virus (HIV), or positive for cytomegalovirus (CMV) DNA, or positive syphilis test.
- Subject who is allergic to the excipients of RC1012 injection or other drugs recommended in the study protocol (e.g., tolimumab, etc.).
- Serious cardiac disease, including but not limited to severe arrhythmia, unstable angina, massive heart attack, New York Heart Association class III or IV cardiac insufficiency, refractory hypertension.
- Persons who have previously received an organ transplant or are preparing to receive an organ transplant (except for HSCT).
- Subject who has received other maintenance therapy drugs after HSCT or who wish to receive other maintenance therapy.
- Subject with the presence of acute GvHD of degree III to IV or extensive chronic GvHD.
- Active neurological autoimmune or inflammatory diseases (e.g. Guillain-Barre Syndrome (GBS), Amyotrophic lateral sclerosis (ALS)).
- Clinically significant active cerebrovascular disease (e.g. cerebral oedema, Posterior Reversible Encephalopathy Syndrome (PRES)).
- Subject with a life expectancy of less than 3 months.

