- Dose-limiting toxicities (DLTs) and maximum tolerated dose (MTD) (Phase I only): Cytokine release syndrome (CRS) will be graded according to the ASTCT 2019 criteria, while other AEs will be graded based on the NCI-CTCAE version 5.0. The frequency and severity of DLTs will be assessed to determine the MTD for the subjects.
  1. **Response Assessment**
- Complete Remission (CR): Bone marrow blasts < 5%; absence of circulating blasts and blasts with Auer rods; absence of extramedullary disease; ANC≥1.0×10^9^/L; platelet count ≥100×10^9^/L;
- CR without MRD (CR MRD^-^): If studied pretreatment, CR with negativity for a genetic marker by RT-qPCR, or CR with negativity by MFC;
- CR with incomplete recovery (CRi): All CR criteria except for residual neutropenia (< 1.0 ×10^9^/L or thrombocytopenia (< 100 ×10^9^/L);
- Morphologic leukemia-free state (MLFS): Bone marrow blasts < 5%; absence of blasts with Auer rods; absence of extramedullary disease; no hematologic recovery required;
- Partial Remission (PR): All hematologic criteria of CR; decrease of bone marrow blast percentage to 5% to 25%; and decrease of pretreatment bone marrow blast percentage by at least 50%;
- Treatment failure: Failure to achieve CR or PR
  1. **Relapse**
- Hematologic relapse: after achieving CR MRD^-^, CR, or CRi in AML patients, the reappearance of leukemic cells in peripheral blood or ≥5% blasts in bone marrow (excluding other causes such as bone marrow regeneration after consolidation chemotherapy), or leukemic cell infiltration at extramedullary sites.
- Molecular relapse: after achieving CR MRD^-^, the reappearance of MRD positivity detected by standard methods [e.g., RT-qPCR or multiparametric flow cytometry (MFC) with a sensitivity of at least 10^-3^].
  1. **Survival**
- Overall Survival (OS): From the date of entry into the clinical study until death from any cause.
- Relapse-Free Survival (RFS):  the time from study enrollment until documented disease relapse, or death from any cause.

1. **ADVERSE EVENT REPORTING**
   1. **Definitions**
      1. **Adverse Event**

An AE is any undesirable sign, symptom or medical condition or experience that develops or worsens in severity after starting the first study treatment in the protocol, even if the event is not considered to be related to the study.

- - 1. **Serious Adverse Event**

A SAE is any adverse event, occurring at any dose and regardless of causality that:

- Fatal
- Life-threatening
- Requires or prolongs hospital stay

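### GRFS counts GvHD of any grade and has no rule for GvHD present at enrollment, although eligibility admits patients with mild GvHD

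*Protocol*

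**What the plan says.** Protocol section 2.2 (Secondary Objectives) gives the only definition of GRFS: "GRFS is the time from study enrollment until documented disease relapse, or death, or GvHD occur from any cause". It names no grade, no acute or chronic type, and no condition of new onset or worsening. Section 6.2 lists the endpoint again with a different starting point, "Relapse-free survival (RFS), GvHD-free relapse-free survival (GRFS), and 2-year overall survival (OS) post-cell infusion", and again without a grade. Section 6.6 (Survival) defines OS and RFS but not GRFS.

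Three eligibility texts bear on GvHD at entry:
- Section 4.1.2, first bullet: "Patients with active grade II to IV acute GvHD or extensive chronic GvHD".
- Section 4.1.2, later bullet, and the only GvHD exclusion in the synopsis: "Subject with the presence of acute GvHD of degree III to IV or extensive chronic GvHD".
- Section 4.1.1, timing: "The subject has received an allo-HSCT within 60-100 days"; and recovery: "The subject has recovered from the toxicity of the prior treatment, i.e., CTCAE toxicity grade <2".

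No criterion requires a patient to be free of GvHD.

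**The concern.** An event-free survival endpoint needs every patient to be event-free at the time origin, or a rule for those who are not. Here the population may include patients who already have one component of the composite, and the protocol has no such rule. Two assessors could score the same patient differently: as an event on the day of enrollment, or as event-free until something changes.

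There is also no severity limit. A short-lived mild GvHD episode therefore ends GRFS exactly as relapse or death does. The Background (section 1) cites an association between higher DNT frequency and less severe GvHD after transplant as a possible benefit of the product. An any-grade event cannot register a shift from severe to mild GvHD, because both count once and alike.

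At stake are the interpretability of GRFS in Part A, which has no control arm, and the sensitivity of the randomized comparison in Part B.

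**Working it through.** **Step 1: who can enter with GvHD.**

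| GvHD at screening | Synopsis | Section 4.1.2, both bullets together |
|---|---|---|
| Acute grade I | admitted | admitted |
| Acute grade II, active | admitted | excluded by the first bullet |
| Acute grade III-IV, active | excluded | excluded |
| Chronic, non-extensive | admitted | admitted |
| Chronic, extensive | excluded | excluded |

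The toxicity-recovery criterion does not change this, since it asks for a grade below 2 and not for absence of GvHD. Acute grade I and non-extensive chronic GvHD are thus admissible throughout. Acute grade II depends on which text is followed.

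**Step 2: the two readings of the definition.**
- *Any GvHD counts.* The admitted patients have the event at time zero.
- *Only GvHD that begins after enrollment counts.* A patient admitted with grade I who later reaches grade IV has had GvHD throughout, and the text does not say whether worsening is an event.

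**Step 3: size under the first reading.** The protocol gives no GRFS rate, no prevalence of GvHD at entry, and no alpha, power, effect size or allocation ratio for Part B. There is no figure to reproduce, and everything below is illustrative.

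*Level.* Let f be the share with GvHD at entry and S the 2-year GRFS in the others. Reported GRFS = (1-f) × S, which is at most 1-f. With S = 60% (assumed) and f = 10, 20, 30% (assumed), this is 0.90 × 60 = 54%, 0.80 × 60 = 48% and 0.70 × 60 = 42%.

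*Contrast.* If f is the same in both arms, each event rate becomes f + (1-f)p, so the difference is (1-f)(p1 - p2). Assumptions:
- 2-year event rates of 60% and 35% among patients free of GvHD at entry.
- 1:1 allocation and two-sided 0.05.
- The 40-60 patients of Part B read as the total, so 20 or 30 per arm.

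Power for two proportions is Φ[(d - 1.96√(2p̄(1-p̄)/n)) / √((p1(1-p1)+p2(1-p2))/n)]. For f = 20% and n = 30: p1 = 0.20 + 0.80 × 0.60 = 0.68, p2 = 0.20 + 0.80 × 0.35 = 0.48, d = 0.20, p̄ = 0.58. This gives (0.200 - 0.250)/0.125 ≈ -0.40, so power is 34.5%.

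The log-rank column is a simulation with 1,500 runs per row, exponential event times, 24 months of follow-up and a hazard ratio of ln 0.65 / ln 0.40 = 0.47 among patients free of GvHD at entry.

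| f | Event rates | Difference (points) | Power, 30 per arm | Log-rank power, 30 per arm | Power, 20 per arm |
|---|---|---|---|---|---|
| 0% | 60.0 vs 35.0 | 25.0 | 49.1% | 51.3% | 34.9% |
| 10% | 64.0 vs 41.5 | 22.5 | 41.3% | 40.0% | 29.2% |
| 20% | 68.0 vs 48.0 | 20.0 | 34.5% | 31.7% | 24.4% |
| 30% | 72.0 vs 54.5 | 17.5 | 28.7% | 24.7% | 20.4% |
| 40% | 76.0 vs 61.0 | 15.0 | 23.6% | 19.1% | 17.1% |

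Dropping patients with GvHD at entry also loses power, because it loses patients: at f = 20% and 30 per arm, power is 40.8%.

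**The case against.** The strongest reply is that the definition speaks of time until GvHD occurs, which naturally describes something that happens after the start. On that reading there are no time-zero events, and the 1-f ceiling and the figures in the table do not apply. This is a fair reading. The protocol does not confirm it, however, and it leaves worsening without a rule.

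A reader might infer that GRFS cannot show a treatment effect at all. The documents do not support that. Part B is randomized, so GvHD at entry is balanced in expectation, and the difference stays above zero for any f below 100%. Nor can it be said that mild GvHD dominates the endpoint, since no prevalence is given.

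Other limits also stand:
- Active acute grade II is not admitted under section 4.1.2, where meeting either bullet excludes. Only the synopsis lets it through.
- The sentence "other AEs will be graded based on the NCI-CTCAE version 5.0" sits in the DLT and MTD item of section 6.3, marked as Phase I only. It does not show that GvHD for GRFS is graded by CTCAE.
- Relapse is measured separately by the 6-month relapse rate and by RFS, neither of which contains GvHD. No dose decision or sample size rests on GRFS.
- Counting any new GvHD can be defended for a product expected to suppress GvHD, and unequal components are common to composites.

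A statistical analysis plan, not at hand, might add grading detail. But the protocol has already written an event definition that sits badly with its own eligibility, so such a plan would have to amend it.

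**Conclusion.** The point holds as a moderate defect in a secondary endpoint. GRFS has no GvHD severity limit and no rule for GvHD present at enrollment, while eligibility admits patients with at least acute grade I or non-extensive chronic GvHD. Under the literal reading, GRFS is capped at 1-f and the Part B difference is multiplied by 1-f. At an assumed f of 20%, the assumed 25 points become 20, and power at 30 per arm falls from about 49-51% to about 32-35%. Under the new-onset reading, worsening has no stated status. Both readings give transient mild GvHD the weight of relapse or death. The mismatch with eligibility follows from the text alone; the sizes rest on assumed prevalence, event rates, allocation and the reading of the Part B total.

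**What to change.** In section 2.2, and added to section 6.6, define the GRFS event as the first of:
- relapse;
- death from any cause;
- GvHD that is new or has worsened after the time origin and reaches acute grade III-IV or extensive chronic.

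That level is the one shared by every exclusion text. It is proposed here only as an endpoint threshold and not as a clinical rule.

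Further changes:
- State that GvHD present at enrollment below that level is not an event.
- Record GvHD at baseline and follow-up on the acute I-IV and limited/extensive chronic grades that eligibility relies on.
- Report any-grade GvHD separately as cumulative incidence, so that the information on mild GvHD is kept.
- Use one time origin for GRFS, RFS and OS, and reconcile the enrollment origin in section 2.2 with the post-infusion wording in section 6.2.

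Separately, the sponsor must reconcile the acute GvHD exclusions (II-IV against III-IV, within section 4.1.2 and against the synopsis), because they determine how many patients enter with GvHD.

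The cost is a change of wording and repeated use of grades already needed at screening. The downside is fewer GRFS events.
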